## Abstract

Emergency Departments (EDs) are high-pressure environments that place significant psychological and physiological stress on both patients and healthcare staff. Despite increasing awareness of stress-related impacts, proactive stress management interventions have limited uptake in healthcare. This proof-of-concept study will evaluate *WeCare*: a 6-week, wearable-integrated, self-guided program grounded in a “Learn–Track–Act” framework to support stress regulation, resilience, and wellbeing. The study will examine four key aspects of implementing the program: (1) feasibility, (2) acceptability and usability, (3) preliminary clinical effectiveness (self-report and physiological outcomes), and (4) preliminary economic impacts. Using a mixed-methods, multiple-baseline N-of-1 design, the program will be trialled with up to 32 participants across four ED-exposed groups: patients with non-severe or severe injuries, patients with acute medical presentations, and ED staff. The intervention includes digital psychoeducation, continuous biofeedback via a smart ring, personalised guidance, and evidence-based self-regulation strategies. Assessments will include standardised questionnaires combined with continuous physiological monitoring via a smartwatch, and interviews. Quantitative outcomes include heart rate variability, sleep patterns, perceived stress, wellbeing, healthcare use, and time off work. Qualitative interviews will explore user experience, usability, and perceived barriers. The findings will inform the refinement of the intervention and co-design of a larger-scale trial, contributing valuable evidence to support low-cost, wearable-enabled proactive mental healthcare in high-stress healthcare environments.

## 1. Introduction

Emergency care settings are high-pressure environments where both patients and healthcare staff experience significant stress. For patients, this stress may arise from acute injuries, distressing symptoms, or the uncertainty surrounding their condition and need for urgent care [1,2]. For healthcare workers, the high cognitive, physical, and emotional demands of emergency care contribute to sustained work-related stress [3,4,5,6,7]. The interactions between these groups can further influence health outcomes, making stress management a critical factor in emergency care.

While stress is an adaptive response to acute challenges, involving physiological and emotional regulation processes, excessive or prolonged stress is detrimental to health [8]. Heightened stress reactivity is linked with increased morbidity and mortality [8], including higher risks of cardiovascular disease, immune dysregulation, and mental health disorders such as post-traumatic stress disorder (PTSD), depression, and anxiety disorder [8,9,10,11]. The ability to adapt and self-regulate, by efficiently modulating emotional and physiological responses to situations, is considered central to mental health and wellbeing [11,12]. This capability influences how a person copes with stress, maintains daily functioning and life roles, and achieves optimal performance [12,13]. Despite increasing recognition of the significant health impacts of excessive or prolonged stress, particularly on mental health [8,14], there remains a lack of effective, scalable, self-directed interventions for patients and healthcare staff exposed to high-stress environments such as emergency care settings.

Acute injuries [15], particularly those resulting from motor vehicle crashes [16], are major contributors to global mental health burden and disability [17,18,19], often leading to significant psychophysiological distress [20,21]. Studies show that up to 50% of individuals with acute injuries remain highly distressed six weeks after injury, increasing their risk of developing PTSD, depression, and anxiety disorders [9,10,22,23]. Dysregulated stress responses and heightened physiological arousal have also been identified as physiological stress markers in those experiencing elevated distress following traumatic injuries [20,24]. Despite its considerable impact, psycho-physiological distress associated with sustaining an injury often goes unrecognised, delaying timely support during a critical window for recovery. The Emergency Department (ED) is a critical setting for recognising acute stress, raising awareness, and initiating early psychological support, particularly for patients with minor-to-moderate injuries for whom the ED may be the only point of care. While physical stabilisation is essential, the psycho-physiological impact of trauma is equally important and should receive the same priority in ED care. Neglecting emotional consequences leaves many patients unprepared to cope, given their central role in holistic and sustained recovery [11].

ED healthcare staff face unique daily stressors, fatigue, and repeated exposure to trauma, which disrupt autonomic and circadian regulation, increasing their vulnerability to chronic stress and burnout [3,4,5,6,7,25,26]. Research has demonstrated dysregulation of stress response systems in this population, including blunted cortisol responses and autonomic imbalance [27,28]. Despite this, there is a lack of proactive and sustainable stress-management strategies that are specifically tailored to this workforce and integrated into routine clinical workflows. This highlights a critical gap in current approaches to supporting staff wellbeing and organisational resilience, both of which are essential for maintaining high-quality, safe patient care [26,29].

Best practice for stress measurement recommends combining subjective self-reported outcomes and objective physiological indicators [30]. The autonomic and circadian systems are central to stress, sleep, and mental health regulation [31,32,33]. Disruptions in these systems are emerging as early markers of poor mental health, offering new targets for personalised intervention [8,34,35,36,37,38]. The autonomic nervous system, in particular, plays a central role in stress regulation and wellbeing. Heart rate variability (HRV), a key biomarker of stress resilience, has been consistently associated with emotional regulation, vulnerability to stress, stress-related and mental health disorders [20,36,37,38], as well as broader health outcomes [39,40]. HRV is also closely tied to sleep quality [41,42], highlighting the interconnectedness of sleep and stress in maintaining health and wellbeing. Wearable sensor technologies now enable real-time, ecological monitoring of stress, sleep, and autonomic and circadian regulation through biomarkers like HRV and sleep parameters [35,43,44,45]. Evidence shows wearable-based lifestyle interventions can improve stress, sleep, and overall wellbeing [46,47,48,49], including within healthcare settings and among healthcare staff cohorts [50,51,52,53]. These personalised, low-cost tools show promise for high-stress settings, though adoption and sustained use remain challenging, highlighting the need for pilot studies to assess feasibility.

This proof-of-concept study aims to address these gaps by introducing a 6-week wearable-integrated program to support stress regulation and wellbeing: “Wearable-enhanced Care to Assist stress Regulation and Empowerment (WeCare)*”*. Aligned with the first three steps of the Sax Institute’s Translational Research Framework [54], the study will evaluate the program’s (i) feasibility (practicality and acceptability), (ii) preliminary effectiveness (clinical and cost-related impacts), and (iii) replicability. To assess replicability, WeCare will be trialled across four vulnerable ED groups: patients with non-severe and severe traumatic injuries, patients with acute medical symptoms, and ED healthcare workers. The program will be co-designed and adapted for key user groups in Australian ED settings, where mental health needs are frequently under-addressed. The study will generate critical pilot data to refine the intervention and guide future large-scale trials.

### Study Objectives

As this manuscript presents a study protocol, the purpose of this section is to outline the planned study design and objectives. The evaluation of the WeCare program based on experiences in real-world ED settings will focus on four key objectives, to inform a subsequent larger trial designed to include more participants and broader ED settings:(1)*Feasibility (practicality of study methods):* Assessing the practicality of recruitment and data collection, adherence/engagement to the program, fidelity of program delivery and use, and program safety.(2)*Acceptability and usability*: Exploring user experience with the program and devices, including perceived benefits, challenges, and suggestions for improvement.(3)*Preliminary clinical effectiveness:* Evaluating changes in psychological health and wellbeing using self-reported outcomes (e.g., stress, mood, and anxiety) and physiological markers (e.g., HRV, sleep quality, and circadian rhythm).(4)*Preliminary economic impact:* Estimating the potential cost benefits/savings of WeCare as an early intervention for vulnerable ED populations.

## 2. Materials and Methods

### 2.1. Participants and Setting

Four groups of participants, including patients and ED healthcare workers in emergency care settings, will be recruited from the ED of Royal North Shore Hospital, a Level 1 Trauma Centre, in Sydney, Australia. Between 3 and 8 eligible participants will be recruited per group (at least 3 participants per experiment) for a total of up to 32 participants. The groups are as follows:*Sample* 1: Patients presenting to the ED with mild-to-moderate injuries (Injury Severity Score, ISS < 15).*Sample* 2: Patients presenting to the ED with severe injuries (ISS ≥ 15).*Sample* 3: Patients presenting to the ED with acute non-traumatic, minor-to-moderate medical complaints (Australasian Triage Scale, ATS category 3–5 = less urgent).*Sample* 4: Emergency healthcare workers exposed to workplace stress.

### 2.2. Design Overview

The study includes three interrelated components: (1) an Experimental component, with nested (2) Co-design and (3) Cost analysis components. Each component will address distinct study objectives and evaluation aspects, [54] using different methodologies, to pilot the 6-week WeCare program in a controlled setting, as illustrated in Figure 1.

#### 2.2.1. Experimental Component

The Experimental component aims to evaluate the *preliminary clinical effectiveness* of the program, the *feasibility of recruitment and data collection methods*, and the *safety of the intervention* (adverse events) across the target participant groups (Figure 1). A series of N-of-1 trials will be conducted, nested in a randomised, concurrent multiple-baseline experiment design across participants with at least three tiers (Figure 2). The study will incorporate both direct inter-subject and systematic replications, with a minimum of three participants (tiers) per replication experiment. The protocol for these trials was guided by the Risk of Bias in N-of-1 Trials (RoBiNT) Scale [55,56]. N-of-1 trials are individual randomised controlled trials in which each participant serves as their own control. This design is well suited for application in heterogeneous conditions [57] like stress-related conditions due to its sensitivity to individual differences. When aggregated, N-of-1 trials can yield population-level treatment estimates comparable to traditional randomised controlled trials [58], but with greater efficiency and cost-effectiveness, as they require fewer participants. Quantitative methods will be used for this experimental component of the study, including patient self-report and physiological data from smart wearables.

**Experimental phases:**

Table 1 and Figure 2 provide a schematic overview of the experimental study design, phases, and timeline. Each single-case experiment, including at least three tiers, begins with a **(i) Baseline phase (usual care)** of 1–3 weeks, with duration randomised for each participant, followed by a **(ii) Intervention phase (WeCare program)** of 6 weeks. A staggered, multiple-baseline design is used: all participants start the baseline at the same time, but the intervention begins at different times (Tiers I–III)—approximately 7 days (end of the 1st week) for Tier I, 11 days (midpoint of the 2nd week) for Tier II, and 15 days (start of the 3 week) for Tier III. This ensures robust within-person controls and reducing external bias. The minimum 7-day baseline allows for the collection of at least five observations, ensuring maximum rigour [59], while accommodating day-to-day variability (e.g., “bad day”) and logistical constraints (e.g., participant availability for an in-person visit). During the Baseline phase, participants will be provided with a *smartwatch* device (Vivoactive 5, Garmin Ltd., Schaffhausen, Switzerland, https://www.garmin.com/en-AU/legal/compliance/, https://www.garmin.com/en-AU/p/1057989/; accessed on 15 October 2025), worn on the wrist for continuous physiological monitoring through the whole study. The device’s display will remain blank, and participants will not have access to any feedback or vital sign data. They will be instructed to continue their daily routines and usual care practices without changes to medication, lifestyle, or activities. To support retention and maintain engagement during the baseline phase, participants will receive one to two brief messages per week acknowledging their data collection and encouraging continued participation. Regular contact of this kind has been shown to improve adherence and reduce attrition in single-case and digital health intervention studies [60].

At the start of the Intervention phase, participants will receive a *smart ring* device (OuraRing4, Oura Health, Oulu, Finland, https://ouraring.com/terms-of-use, https://ouraring.com; accessed on 15 October 2025), which will serve as their companion device for the *WeCare* program. Unlike the smartwatch, the smart ring allows participants to view their physiological data in real time through an associated app and provides personalised guidance to support behavioural and lifestyle modifications. Each of the above phases will begin with an in-person session that includes participant education, device setup, and usage instructions. Alternatively, this session may be delivered via telehealth or through a pre-recorded video, with the device mailed or couriered to participants. Following the intervention, an optional **(iii) Extension phase** of 2 weeks will be offered, allowing participants to experience the program using the smartwatch as an alternative wearable. This phase will be an integral part of the “acceptability” evaluation conducted during the co-design component and is not intended to test effectiveness. Follow-up assessments will be conducted at 3 and 6 months post-intervention.

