#### 2.2.3. Cost Analysis Component

The Cost analysis component aims to evaluate the *preliminary cost benefits* of implementing the WeCare program by quantitatively assessing changes in healthcare use and time off work (Figure 1). In this preliminary study, this data will be obtained through self-report measures, including participant diaries on frequency of healthcare visits, medication use, and number of sick leave days taken. While self-reporting provides an accessible and low-burden approach for early-stage evaluation, it will also inform the feasibility of incorporating objective cost and utilisation data (e.g., administrative records) in future larger-scale trials. It will examine whether the initial investment results in cost savings, helping to determine if the program is a viable, low-cost, and sustainable solution for improving mental wellbeing and resilience in emergency care settings.

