#### 2.6.4. Cost Benefits

A nested Cost analysis of the WeCare program will be conducted using weekly self-report diaries collected throughout the study. Data will include *healthcare utilisation* (e.g., medical appointments, hospital visits, treatments, medications, and diagnostics) and *work-related costs* (e.g., time off work due to stress, injury, or illness). The analysis will assess whether the wearable-based intervention reduces healthcare use and work absenteeism. This will inform the economic benefits of implementing the WeCare program as a scalable solution.

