**Figure 3 sensors-26-00104-f003:**
[figure not shown]
WeCare program: weekly themes, suggested activities, and reflection prompts.

**Table 1 sensors-26-00104-t001:** Detail of experimental phases.

Phase	When It Starts	How Long	Device Used	What Happens
Baseline (Usual care)	*Sample* 1 and 3: 0–2 weeks post-ED care. *Sample* 2: 4–6 weeks post-ED care. *Sample* 4: Any time.	1–3 weeks (7, 11, 15 days by tier)	“Blinded” smartwatch (wrist device)	- In-person onboarding. - Wear smartwatch daily. - Smart ring sized for next phase. - Continue usual care, no changes. - Daily diaries and weekly surveys.
WeCare Program (Intervention)	After baseline phase ends	6 weeks (staggered by tier)	“Blinded” smartwatch Smart ring	- In-person onboarding. - Continue smartwatch monitoring. - Start intervention using a digital health platform and a smart ring as companions to track real-time physiological data and receive personalised education/feedback.
Optional Extension (Device testing)	After intervention phase ends	2 weeks	“Blinded” smartwatch	- Smartwatch (instead of smart ring) as intervention companion. - Test delivery method only. - Part of qualitative, co-design acceptability analysis.

**Table 2 sensors-26-00104-t002:** Participants’ inclusion and exclusion criteria.

Participant Group	Inclusion Criteria	Exclusion Criteria

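### The no-change instruction on medication is stated for the usual-care baseline only, so a phase difference in medication use cannot be attributed to WeCare

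*Protocol article*

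**What the plan says.** Section 2.2.1 (Experimental phases) describes the baseline as usual care and says of participants in that phase: "They will be instructed to continue their daily routines and usual care practices without changes to medication, lifestyle, or activities". Table 1 gives the same condition in its Baseline row: "Continue usual care, no changes". The intervention row carries the monitoring forward ("Continue smartwatch monitoring") but has no line on usual care or medication. Neither does the program description in Section 2.5.

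For Samples 1 and 3, Table 1 places the start of baseline at "0–2 weeks post-ED care". Sample 2 starts at 4–6 weeks and Sample 4 at any time.

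Medication is also an outcome. Section 2.2.3 takes the cost data from "participant diaries on frequency of healthcare visits, medication use, and number of sick leave days taken". Section 2.6.4 defines healthcare utilisation to include "medical appointments, hospital visits, treatments, medications, and diagnostics" and asks whether the intervention reduces it. Section 2.4 says that cost data are collected weekly throughout the study. The comparison is within person: "N-of-1 trials are individual randomised controlled trials in which each participant serves as their own control".

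**The concern.** There are two linked problems.

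First, the label and the instruction do not sit easily together. For someone recently treated in an ED, usual care may itself include a change in medication, if only because a course of treatment ends. Such a participant may be unable to satisfy both halves of the sentence as worded.

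Second, the condition is stated for one phase only. If participants follow it, medication use is observed under a no-change instruction in baseline and without one afterwards. The cost analysis would then compare two periods that differ in the program and also in a stated rule on the outcome being counted. What is at stake is the reading of medication use as a preliminary saving, or as a preliminary cost, of WeCare.

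**Working it through.** The plan gives no figure to reproduce. The check is of timing and of what the design can identify.

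**Inputs**
- Baseline length by tier: 7, 11 or 15 days (Table 1).
- Intervention length: 6 weeks, 6 × 7 = 42 days (Table 1).
- Phase in which the no-change instruction is stated: baseline only (Section 2.2.1 and Table 1).
- Comparator: the participant's own baseline (Section 2.2.1); there is no parallel control group.
- Cost diary: weekly, in both phases (Section 2.4).

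**Step 1: days under the instruction, as written**

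| Tier | Baseline days | Intervention days |
|---|---|---|
| I | 7 of 7 | 0 of 42 |
| II | 11 of 11 | 0 of 42 |
| III | 15 of 15 | 0 of 42 |

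**Step 2: can the two be separated within a person?** Let b be the participant's baseline length (7, 11 or 15). Let P(t) = 1 when the program is running (t > b) and 0 otherwise. Let I(t) = 1 when the instruction is in force (t ≤ b) and 0 otherwise. Then I(t) = 1 − P(t) on every day, whichever b was drawn. If expected medication use is a + βP + γI, substitution gives (a + γ) + (β − γ)P. Only β − γ can be estimated. The program effect β cannot be isolated from the instruction effect γ.

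**Step 3: does the staggering help?** It allows comparison between tiers on the same study day. On days 8–11, Tier I is in the program while Tiers II and III are in baseline. On days 12–15, Tiers I and II are in the program and Tier III is not. In both windows the tiers already in the program are also those no longer under the instruction. The between-tier contrast is β − γ again. Randomising b guards against events tied to calendar time, not against something that switches at each participant's own start.

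**Step 4: direction.** The wording asks for no change, which holds medication at its current level, high or low. If it delays the reduction of medication begun around the ED visit, a later fall looks like a saving. If it delays new medication, a later rise counts against WeCare. The sign of γ is not fixed by the documents.

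**Step 5: who is most exposed.** For Samples 1 and 3, baseline starts between day 0 and day 14 after ED care. The instruction therefore ends between day 0 + 7 = 7 and day 14 + 15 = 29 after ED care. That medication is more likely to change in this window than later is an assumption; the documents give no figure.

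**Step 6: can the diary resolve it as described?** Assume diary weeks run from the first baseline day. The Tier II switch falls at 11/7 = 1.57 weeks and the Tier III switch at 15/7 = 2.14 weeks, both inside a diary week. A weekly count without dates cannot place a change in the right phase for those tiers.

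**The case against.** The strongest reply is that the sentence is the ordinary request, in a no-intervention baseline, not to alter anything because of the study. It is addressed to participants, and care by their treating team is part of what they are told to continue. That reading is plausible and may be the intended one, but the text does not say so. If it is meant, it is easily stated, and it would apply equally well in both phases.

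A second reply is that silence in the intervention row may reflect condensation, since a journal article shortens the full protocol. This stands in part: the article nowhere says that medication may change freely during the program. However, it gives the condition twice, both times for baseline, in a table that sets the phases out row by row. As written, the condition ends with baseline.

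A reader might also infer more than the documents support:
- **Time off work and healthcare visits.** The instruction does not name them, and usual care is expressly to continue.
- **Lifestyle and activity.** The instruction names these, but WeCare "provides personalised guidance to support behavioural and lifestyle modifications", so a phase difference there is largely the intended treatment contrast.
- **A known direction of bias.** Unchanged is not the same as reduced (Step 4).
- **Protocol breaches or a risk to participants.** Both need a strict reading that the wording does not require.

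The cost outcomes are described as preliminary and medication is already recorded weekly. Both points limit the weight of the problem without removing it.

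**Conclusion.** The point holds for medication use. Nothing in the program description presents a change in medication as part of WeCare, so the defence available for lifestyle and activity does not apply. As the article stands, the end of the instruction and the start of WeCare coincide in all three tiers. A phase difference in medication use, up or down, cannot be attributed to the program.

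This rests on two assumptions: that the instruction is in fact limited to baseline, as both places state it, and that at least some participants act on it. The size of the bias cannot be derived from the documents. The concern is greatest for Samples 1 and 3 because of their early start, and weaker for Samples 2 and 4. It should not be extended to the primary outcomes: an effect on HRV or sleep through medication is conceivable, but the documents give nothing with which to establish it. The point deserves correction because the remedy is small, but it does not undermine the study as a whole.

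**What to change.** 1. The clinical investigators should reconcile the usual-care label with the no-change wording on medication in Section 2.2.1 and Table 1, for example by saying whether it means only that nothing is to be changed on account of the study. This review proposes no clinical rule.
2. State the resulting condition on medication and usual treatment in the same words for baseline and intervention, leaving WeCare-related behaviour as the planned difference.
3. Add to the existing weekly diary the date of each change in medication or treatment, and mark these dates on the participant plots.
4. If the baseline-only instruction is kept, do not report phase differences in medication use as program effects or savings.

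The cost is one reworded sentence, changes to two rows of Table 1 and a date field in the diary. Baseline values may vary slightly more from day to day.
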